### Sample size

It was reported that the rate of poor outcome of patients with a hemorrhage volume above 30 ml who received craniotomy is about 49% to 67% [19,21,24]. Previous studies showed that the MIS could decrease the rate of poor outcome by about 7% to 22% [19,21] compared with craniotomy. We assume that the neuroendoscopy and stereotactic aspiration can reduce the rate of poor outcome from 58% to 51%, and a sample size of 2203 patients will be required with a significance level of 5% (2-sided) and a power of 80%. In consideration of ensuring the quality of research, the sample size is enlarged to 2448 (816 In each arm).

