### Statistical analysis

The “intension to treat” analysis will be applied in this study. The descriptive analysis of all measurement data is implemented using mean, standard deviation, median, interquartile range, maximum and minimum indicators; the descriptive analysis of count data is implemented using index such as rate, ratio and RR. The primary analysis will be a simple categorical frequency comparison for unfavorable outcome by means of Chi-square test, so will the categorical data of secondary outcomes. The continuous outcomes will be analyzed by t-test. The log-rank method will be used in the analysis of time- to-event type of outcomes. Subgroup analysis stratified by age, location of hematoma, volume of hematoma, GCS at hospitalization, with/without intraventricular hemorrhage, and midline shift is preplanned. Statistical inference is conducted using the above-mentioned hypothesis testing method and confidence interval may also be used when necessary. P values ≤0.05 (α = 0.05) will be considered statistically significant. All statistical analysis is performed using SAS or SPSS statistical software.

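### For six preplanned subgroup factors the article offers only chi-square, t-test and log-rank at P≤0.05; none tests whether the treatment effect differs between strata, and no exploratory label is attached

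*Protocol article*

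**What the plan says.** All of the relevant text is in the Statistical analysis section of the protocol article.

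- Primary test: "The primary analysis will be a simple categorical frequency comparison for unfavorable outcome by means of Chi-square test". Categorical secondary outcomes use the same test, continuous outcomes a t-test and time-to-event outcomes the log-rank method.
- Subgroups: "Subgroup analysis stratified by age, location of hematoma, volume of hematoma, GCS at hospitalization, with/without intraventricular hemorrhage, and midline shift is preplanned".
- Inference, in the next sentence: "Statistical inference is conducted using the above-mentioned hypothesis testing method and confidence interval may also be used when necessary".
- Threshold, in the sentence after that: "P values ≤0.05 (α = 0.05) will be considered statistically significant".

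The section gives no cut-points, no rule for comparing strata, no interaction test, and no remark on the status of subgroup results. The inference and threshold sentences are worded for the whole section. They follow directly on the subgroup sentence and exempt nothing.

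**The concern.** A subgroup analysis asks whether the difference between techniques depends on a patient characteristic. A chi-square test within older patients and another within younger patients do not answer that. Each asks whether there is a difference in its own stratum, at reduced power. If one gives P≤0.05 and the other does not, the effects may still be identical.

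The trial's design effect makes this pattern especially frequent. A stratum holding half the patients has power close to 50%, and two tests with equal power disagree most often when that power is 50%.

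At stake is how the subgroup results are read, not the primary result. If the trial finds a uniform benefit, a table of stratum P values at 0.05 would very probably contain at least one contrast that looks as if a technique works in one kind of patient and not in another.

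**Working it through.** **Inputs.** From Sample size: poor-outcome rates of 58% (craniotomy) and 51% (each of the other two arms), two-sided 5%, 80% power, 2203 patients required, 2448 planned (816 per arm). From Statistical analysis: six factors, the chi-square test, P≤0.05. Assumptions of this check, because the article gives no figures for them: two levels per factor; splits of 50/50 (also 30/70); factors independent of each other and unrelated to the outcome rate.

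**Step 1: reproduce the sample size.** For a three-group chi-square test (2 df) with n per arm, the noncentrality is n × Σ(pᵢ − p̄)² / [p̄(1 − p̄)].

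- p̄ = (0.58 + 0.51 + 0.51)/3 = 0.5333
- Σ(pᵢ − p̄)² = 0.04667² + 2 × 0.02333² = 0.003267
- Noncentrality per patient per arm = 0.003267 / (0.5333 × 0.4667) = 0.013125
- 80% power needs n = 734.07 per arm, so 3 × 734.07 = 2202.2, rounded up to 2203

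The stated 2203 is reproduced, which points to the three-group test as the planned primary test. 2203/0.90 = 2447.8 gives 2448, so a 10% allowance is a plausible source of the larger figure, but the article does not state one.

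**Step 2: power within a stratum, same effect everywhere.** The same formula at smaller n gives:

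| Stratum | n per arm | Power |
|---|---|---|
| 50% of 816 | 408 | 53.3% |
| 50% of 734 | 367 | 48.8% |
| 30% of 816 | 245 | 34.2% |
| 70% of 816 | 571 | 68.7% |

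**Step 3: one factor, chance that the two strata disagree.**

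- 50/50 split, 816 per arm: 2 × 0.533 × 0.467 = 49.8%
- 50/50 split, 734 per arm: 2 × 0.488 × 0.512 = 50.0%
- 30/70 split, 816 per arm: 0.342 × (1 − 0.687) + 0.687 × (1 − 0.342) = 55.9%

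**Step 4: six factors.** The six factors divide the same patients, so the single-factor chances cannot be multiplied. Simulation with 816 per arm (4,000 trials per setting) gives:

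| Result in a trial | No effect, 50/50 | No effect, 30/70 | Uniform 58/51/51, 50/50 | Uniform 58/51/51, 30/70 |
|---|---|---|---|---|
| At least one factor with discordant strata | 31.9% | 33.7% | 86.6% | 92.6% |
| At least one of 12 stratum tests at P≤0.05 | 32.4% | 34.0% | 94.8% | 94.8% |
| At least one of six interaction tests at P≤0.05 | 27.0% | 26.5% | 25.6% | 27.4% |
| At least one of six interaction tests at 0.05/6 | 5.1% | 4.6% | 4.9% | 5.6% |

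Under the uniform effect, a significant stratum test is a correct finding of benefit. The error lies in the first row, where strata that share one effect appear to differ.

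**Step 5: other ways of counting.** Twelve independent tests under no effect would give 1 − 0.95¹² = 46.0%, but the tests overlap, so 32–34% is the relevant figure. Running all three pairwise comparisons in each stratum raises it to about 63%. Six independent interaction tests give 1 − 0.95⁶ = 26.5%, in line with the simulation.

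**The case against.** The strongest objection is that this is silence in a condensed article. Cut-points, interaction models and the status of subgroup results are commonly left to the full protocol or the SAP, and neither is shown. The inference sentence is general, and the article never says that strata will be compared by their P values.

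Part of this stands. A reader might infer that the trial has chosen stratum-wise testing in place of interaction tests. The document does not support that: it neither mentions nor excludes interaction tests. A reader might also take the 86% as the chance of a false subgroup claim. It is the chance of a discordant pattern of P values, which becomes a false claim only if someone reads it as effect modification. The study objectives include no subgroup aim, and the Discussion's remark that individual treatment selection is difficult is background on the field.

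The objection does not remove the point. The article is not silent on method: it says "Statistical inference is conducted using the above-mentioned hypothesis testing method" immediately after the subgroup sentence, and the methods named above that sentence cannot address effect modification as listed. Someone following the text would produce stratum-wise tests at 0.05 with no caution attached.

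A further objection is that, with no effect anywhere, the gain from interaction testing is small: about 27% against 32–34%. That is correct. The gain is large when there is a uniform effect, where interaction tests give about 26–27% against 86–93% for discordant strata.

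**Conclusion.** The point holds in a limited form. As written, the only tests available to the six-factor subgroup analysis do not test whether the effect differs between strata, and no exploratory label is attached.

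With a uniform 58% versus 51% effect, at least one factor shows discordant significance in about 86% of trials (about 93% with 30/70 splits). With no effect anywhere, at least one three-group stratum test reaches P≤0.05 in about 32–34%. These figures assume two-level, independent factors unrelated to the outcome rate. The single-factor figure of about one half is stable: it is the same with 734 or 816 per arm and rises to 56% with 30/70 splits.

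Two stronger conclusions a reader might draw are not supported. False stratum findings are not more likely than not when no treatment differs, unless all pairwise comparisons are tested. Nor would interaction tests alone settle the matter, since six of them at 0.05 leave about 26% familywise error.

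The primary analysis and sample size are not affected. This should be corrected, but it does not threaten the trial's main result.

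**What to change.** Add to Statistical analysis, or confirm in the SAP, wording such as: for each of the six factors, effect modification on the primary outcome will be assessed by a treatment-by-factor interaction test in a logistic model; stratum-specific estimates with 95% confidence intervals are descriptive; all subgroup results are exploratory. If a confirmatory reading is wanted, test each interaction at 0.05/6 = 0.0083, which brings the familywise error to about 5%.

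Leaving out stratum P values and keeping age, hematoma volume, GCS and midline shift continuous in the interaction model are optional preferences, not corrections.

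The cost is a few lines of text and fewer nominally significant subgroup results. No change to sample size, data collection or the primary analysis is needed.

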### Data and safety monitoring

An independent data and safety monitoring board (DSMB) will monitor the safety and efficacy of this trial. The DSMB consists of neurosurgeons, neurologists, radiologists, statisticians, and data managers. Members of the DSMB will meet in person twice a year to review the trial data. Interim analyses will be conducted. The DSMB will stop the trial if one of the treatments shows advantage or higher incidence of severe adverse effect (SAE) than the other two at a very high significance level (differences of more than 3 SD). The adverse event (AE) is any undesirable syndrome of enrolled patients happens during this study. The SAE is defined as death and persistent vegetative state. Both AEs and SAEs will be recorded in the CRF in detail. If SAE happens, researchers must notify it to the DSMB in 24 hours.

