The treatment of sICH is still controversial among neurosurgeons and neurologists. The focus of debate is whether evacuation of hematoma would be able to improve the prognosis of patients. Previous studies showed that the removal of hematoma might reduce nervous tissue damage, possibly by relieving local ischemia and removing noxious chemicals [6-8]. Several studies aiming to explore the efficacy of surgery for patients with sICH have been carried out but showed different results. In 1961, Mickissock and colleagues published the first prospective randomized controlled trial. Their results showed that patients treated surgically had worse outcome than the patients in the conservative group [9]. Another influential study is the STICH series trials, which concluded that there was no overall benefit of early surgery for patients with supratentorial sICH compared with conservative treatment [10,11]. Some researchers attributed this to additional surgical traumatization. In order to reduce surgical traumatization, some minimally invasive techniques have been used in hematoma evacuation. These minimally invasive techniques include stereotactic aspiration and neuroendoscope assisted surgery. The stereotactic aspiration guided by CT was successfully applied for hematoma evacuation by Backlund and collogues at 1978, and this minimally invasive surgery was further improved by some scholars [12]. It was reported that the stereotactic aspiration combined with fibrinolytic drugs could be more effective in hematoma evacuation than aspiration alone [13]. Another category of minimally invasive technique is neuroendoscope. Auer et al. reported that neuroendoscope could be applied to hematoma evacuation, but a subsequent randomized controlled trial showed that the outcome of surgical patients with putaminal or thalamic hemorrhage was not better than medical treatment [14,15]. Recently, a lot of studies exploring the efficacy of minimally invasive surgery (MIS) compared with conservative craniotomy or medical treatment were carried out, but none of them provided sufficient evidence regarding the choice of treatment [16-20]. A further meta-analysis showed that patients with supratentorial intracerebral hemorrhage might benefit more from MIS than other treatment options [21]. Though MIS seems less invasive than the traditional craniotomy, it was reported that the incidence of some complications (e.g. rebleeding and infection) was higher than craniotomy. In addition, with assistance of neuronavigation and operative microscope, hematoma evacuation by craniotomy could also be minimally invasive [22,23]. Until now, there is no randomized controlled trial comparing the efficacy of neuroendoscopy, stereotactic aspiration and craniotomy in patients with spontaneous intracerebral hemorrhage except a small-scale trial by Cho and colleges. Thus, a large-scale clinical trial is necessary to provide robust evidence for clinical practice by assessing the safety and efficacy of different surgical methods including neuroendoscopy, CT-stereotactic aspiration and neuronavigation-assisted craniotomy for sICH. Here we designed a randomized, assessor-blinded, parallel-group, controlled, multi-center clinical study termed minimally invasive surgery treatment for patients with spontaneous supratentorial intracerebral hemorrhage (MISTICH).

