#### Secondary outcomes

The secondary outcomes include: mortality at 30 days, and 6 months after surgery; neurological functional status of 6 months after surgery measured by GOS, Modified Rankin Scale (mRS), Barthe index (BI), and National Institutes of Health Stroke Scale (NIHSS) separately; complications include rebleeding, ischemic stroke, intracranial infection; days of hospitalization.

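### The SAE definition covers only death and persistent vegetative state, so rebleeding, intracranial infection and ischemic stroke short of those outcomes trigger neither the 24-hour DSMB notice nor the SAE limb of the stopping rule

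*Protocol article*

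**What the plan says.** The Data and safety monitoring section of the protocol article sets up two tiers of event. The lower tier is broad: "The adverse event (AE) is any undesirable syndrome of enrolled patients happens during this study". The upper tier is closed: "The SAE is defined as death and persistent vegetative state". Both tiers go on the case report form ("Both AEs and SAEs will be recorded in the CRF in detail"), but only the upper tier has further consequences.

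- Prompt notice: "If SAE happens, researchers must notify it to the DSMB in 24 hours".
- Stopping: "The DSMB will stop the trial if one of the treatments shows advantage or higher incidence of severe adverse effect (SAE) than the other two", with a threshold of more than 3 SD.

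The same section gives the DSMB a general remit over safety and efficacy, has it meet twice a year to look at the trial data, and provides for interim analyses.

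Elsewhere, the Background says of minimally invasive surgery that "the incidence of some complications (e.g. rebleeding and infection) was higher than craniotomy". The Study objective section makes the safety of the techniques the secondary objective. The Secondary outcomes section says that "complications include rebleeding, ischemic stroke, intracranial infection". The CT scan section schedules scans at 1, 3 and 7 days after operation and defines rebleeding by hematoma volume.

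**The concern.** The harms that the protocol itself expects to differ between techniques are not the harms that its stated safety triggers look at. A rebleed, infection or new stroke that leaves the patient alive and not vegetative counts as an ordinary adverse event, however severe it is. The only handling stated for it is an entry on the case report form.

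The two events that do count as SAEs are the worst results on the scale used for the primary outcome. The SAE comparison is therefore largely a second look at the efficacy endpoint and adds little that is specific to a surgical technique.

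At stake is how quickly, and under what stated rule, an excess of procedural complications in one arm would be acted on. This matters while patients are still being randomised, because a final comparison of complication rates comes too late for them.

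**Working it through.** The protocol gives no figure for complication rates, so the check is mainly a reading of the sections against each other.

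**Step 1. Classify each event by the stated definition.**

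| Event | SAE as defined? | 24-hour notice? | Counts in SAE limb of stopping rule? |
|---|---|---|---|
| Death | yes | yes | yes |
| Persistent vegetative state | yes | yes | yes |
| Rebleeding, patient alive and not vegetative | no | no | no |
| Intracranial infection, same condition | no | no | no |
| Ischemic stroke, same condition | no | no | no |
| Any of the three ending in death or vegetative state | yes, through that outcome | yes | yes |

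All three listed complications are outside both mechanisms unless they end in one of the two defined events.

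**Step 2. See whether the other limb covers them.** The stopping rule also refers to one treatment showing an advantage, but names no endpoint for it. It neither clearly includes nor clearly excludes complications, so it cannot be counted on to cover them.

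**Step 3. Compare the SAE definition with the primary outcome.** The Primary outcome section combines death with dependency on the Glasgow Outcome Scale. Death is a component by name. Vegetative state is the most extreme dependency, so it is a component under any sensible cut-off (the article does not print one). Both SAE events thus lie inside the primary outcome.

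**Step 4. Compare timing.** The CT scan section has rebleeding measurable on days 1, 3 and 7. Table 1 first records the Glasgow Outcome Scale at one month. Deaths apart, the stated rule uses the later information and not the earlier.

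**Step 5. Can a size be given?** Only under assumed rates. With n per arm and mean rate p̄, a pairwise comparison of rates a and b has z = (b − a) / √[p̄(1 − p̄) × 2/n]. The Sample size section gives 816 per arm; half of that is 408. For example, 5% versus 10% at n = 408 gives 0.05 / √(0.075 × 0.925 × 2/408) = 2.71.

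| Assumed rates | n = 408 per arm | n = 816 per arm |
|---|---|---|
| 5% v 8% | 1.74 | 2.46 |
| 5% v 10% | 2.71 | 3.83 |
| 3% v 10% | 4.06 | 5.74 |

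Against a threshold of 3 (nominal two-sided p about 0.0027), the answer depends wholly on the assumed rates and the time of the look. The table also does not model the written rule, which sets one arm against the other two. With 10% in one arm and 5% in two pooled arms at 408 per arm, p̄ = (0.10 + 2 × 0.05)/3 = 0.0667 and z = 0.05 / √[0.0667 × 0.9333 × (1/408 + 1/816)] = 3.3. No single figure from this range is evidence about this trial.

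**The case against.** The strongest reply is that the DSMB is not confined to the SAE rule. It monitors safety in general, sees the trial data twice a year and has interim analyses. Adverse events are recorded in detail, and completed forms are to reach the trial secretary without delay. A condensed article may also leave other reporting routes to the full protocol. In the article SAE stands for *severe* adverse effect: it marks the tier that triggers DSMB notice and does not say that other events are not serious. All of this stands, and it rules out three stronger readings.

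- *That these complications never reach the DSMB.* They may be seen at the twice-yearly review, and those ending in death or vegetative state are captured at once.
- *That patients would go on being randomised until an excess of complications shows up as deaths.* This assumes the 3-SD rule is the only ground on which the DSMB may act, which the section does not say.
- *That the 3-SD boundary would be crossed unnoticed.* For 5% versus 10%, z is 2.71 at half enrolment, which is below 3. The value 3.83 arises only at full enrolment, when stopping spares nobody from randomisation. By the same pairwise formula z reaches 3 at n = 9 × 2 × 0.075 × 0.925 / 0.05² ≈ 500 per arm, about 1,500 of 2,448 patients, and the rates are invented.

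The reply does not close the narrower gap. The article itself states the definition, the notice rule and the stopping rule, so this is not a detail left to another document. A discretionary six-monthly look is also not the same as prompt notice and a stated comparison for risks that the protocol has already named.

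**Conclusion.** The concern holds in a limited form. As written, none of the three listed complications triggers the 24-hour notice or counts in the SAE limb of the stopping rule unless it ends in death or persistent vegetative state. This sits badly with the Background, the secondary objective and the list of secondary outcomes.

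The conclusion rests on reading the SAE definition as closed, which is how it is worded, and on vegetative state counting as dependency in the primary outcome. It does not rest on any assumed event rate, and no numerical effect on stopping can be claimed.

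The primary endpoint and its analysis are untouched, and the complications are collected and compared at the end. This is a worthwhile correction to safety monitoring, best made while enrolment continues. It is not a defect that undermines the trial.

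**What to change.** Keep the present SAE definition and add a short list of named safety events: rebleeding, intracranial infection and ischemic stroke. For these:

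1. State a prompt notice period to the DSMB.
2. Tabulate them by arm at each twice-yearly meeting.
3. Include them in the between-arm harm comparison, so that the stopping text covers them explicitly.
4. State which rebleeding definition applies: the volumetric one in the CT scan section, or that definition with a stated clinical-symptom qualifier. The volumetric definition also counts a change of under 5 ml from before to after surgery, so an incomplete evacuation can qualify. The choice affects how many reports arise.

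Rewriting the SAE definition to take in disability or prolonged stay is not advised. Dependency is the other component of the primary outcome, assumed at 51% to 58% together with death. Such criteria would increase the overlap with efficacy and could bury the technique-specific signal.

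The cost is an amendment to the protocol and case report form wording, more expedited reports from the 20 centers, and more comparisons for the DSMB to weigh, with a correspondingly greater chance of a false alarm. The complications are already study outcomes, so little new data collection is needed unless a symptom qualifier is added.

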### Study organization

This study is initiated by Department of Neurosurgery in West China Hospital, Sichuan University. West China Hospital is a 4300-bed, superior large comprehensive teaching and researching hospital in China. The Department of Neurosurgery, founded in the 1950s, is one of the earliest neurosurgery specialty wards in China and the largest neurosurgery unit in Southwestern China. A total of 20 centers will participate this study, and the list of centers is showed in the acknowledgement.

